#### 3.1.2. Test of Noninferiority (Secondary Endpoint) for G2a and G2b Comparison

The sample size for the assessment of the noninferiority of G2b in front of the G2a arms will be based on the REBORNE scale. A total sample size of 72 participants with 36 in group G2a and 36 in group G2b will achieve more than 90% power to establish the noninferiority using a one-sided 2.5% alpha level. The margin of noninferiority is 10% on the ratio of means, assuming that the true ratio is 1.0 (i.e., G2a and G2b have the same effect). The coefficients of variation of both groups are assumed to be around 0.1349 based on internal data, with a mean of 0.113 and a SD of 0.815 [23].

All sample size calculations have been performed using the nQuery v7.0 validated software [24].

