Difficulties are encountered to define the sample size, the randomization procedure, and the study design due to the scarcity of comparable studies. A multicentric, randomized study was planned to ascertain that, having standardized the ATMP in four countries (France, Germany, Italy, and Spain), patients could receive analogous treatment from different GMP facilities in different hospitals. First, this requires agreement of the national regulators, and a voluntary harmonization procedure (VHP) was launched within the European Union [35]. Second, stratification by production centre has been planned for the randomization procedure, and this will enable to similarly assess cell production in all centres.

The sample size calculations have been based on success rates with ICA as the control on bone healing multicentric trials [8]. Scarcity of references (both for controls and technology under evaluation) is observed in the literature. Of note, no direct head-to-head comparison in a well-designed randomized clinical trial has been previously conducted with ICA and MSCs. In this scenario with uncertainties in the final success rates and in the final delta of superiority, it is also noted that very small rate changes in those assumptions may have an impact in the actual statistical power. However, clinical relevance of the potential superiority of the technique would not be clearly defined unless the success rate is clearly higher. Furthermore, other reasons for failure besides the augmentation with the ATMP need to be excluded by the clinical trial committee. Foreseen reasons of failure unrelated to the ATMP include unstable fixation or other mechanical issues, inappropriate placement of the biomaterial with cells or the bone autograft (on-lay apposition instead of the recommended in-lay application), or intraoperative complications (intraoperative fractures or other distortion). Those cases will not be evaluated by PP although ITT analysis will be performed. Justification of the noninferiority of the lower versus the higher dose of hBM-MSCs is also a potential limitation of the study. A pragmatic approach was agreed in a noninferiority margin of 10% consolidation rate based on the differences between ICA controls and technologies designed to enhance bone healing in retrospective [26] and prospective [8] studies. This difference of 10% could be considered clinically irrelevant.

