**Figure 2 fig2:**
[figure not shown]
Flow diagram of the ORTHOUNION clinical trial.

**Table 1 tab1:** Outcome measure and statistical analysis table.

Objective	Outcome measure	Time points of evaluation	Statistical analysis
Principal objective: to determine if the combined treatment of the ATMP, hBM-MSC + biomaterial (G2), is superior to the control, iliac crest autologous graft (G1), to obtain radiological and clinical bone consolidation	Bone consolidation is considered achieved when meeting the three following criteria: (1) Radiographic bone bridging: new bone formation across the fracture site visible in 3/4 cortices, on at least 3/4 views (2) Clinical healing: pain less than 3 in a NRS (0 to 10) for pain during full weight bearing and without weight bearing [36] (3) No further surgical major intervention (nail replacement, plate replacement, or replacement of all components of the previous surgery)	At 12 months after surgery	Superiority (target delta of 20%). Percentages will be estimated using a log-binomial regression model including the treatment, manufacturing site, and baseline value of the REBORNE scale as covariates. If unexpectedly the model does not fit, the Poisson long-link distribution function with a robust variance estimator will be used instead.

SO1: to determine if the low dose of hBM-MSC + biomaterial (G2b) is noninferior to high dose of hBM-MSC + biomaterial (G2a) to obtain radiological consolidation	Score calculated in xR images from REBORNE radiological scale following the formula: REBORNE score = ∑(internal, external, anterior, and posterior cortical value^∗^)/(4 × number of evaluable cortices)	At 12 months after surgery	Noninferiority (target delta of 10%). A log-transformed data of the values will be used in a mix model for repeated measurements, only if the primary outcome reaches statistical significance. Differences between arms will be estimated through adjusted means, standard errors, and its 95% CI

SO2: to compare the percentage of bone consolidation between G1 versus G2 and G2a versus G2b treatment arms	As defined in the principal objective	(i) G1/G2: at 6 and 24 months after surgery (ii) G2a/G2b: at 6, 12, and 24 months after surgery	Fisher's exact test

SO3: to compare the radiological consolidation between G1 versus G2 and G2a versus G2b treatment arms	As defined in SO1	At baseline and 6, 12, and 24 months after surgery	*t*-test or Mann–Whitney test

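### The dose noninferiority margin is justified as a 10% consolidation rate but tested as a 10% ratio of mean REBORNE scores, and nothing in the article links the two

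*Protocol article*

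**What the plan says.** Section 3.1.2 sizes the low-dose (G2b) versus high-dose (G2a) comparison on the radiological score: "The sample size for the assessment of the noninferiority of G2b in front of the G2a arms will be based on the REBORNE scale". It sets the margin there: "The margin of noninferiority is 10% on the ratio of means, assuming that the true ratio is 1.0". It plans 36 per arm, more than 90% power, one-sided alpha 2.5% and a coefficient of variation (CV) of 0.1349.

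Table 1 agrees in its SO1 row. The outcome is a "Score calculated in xR images from REBORNE radiological scale following the formula" given there, at 12 months, and the analysis entry reads: "Noninferiority (target delta of 10%). A log-transformed data of the values will be used in a mix model for repeated measurements". SO1 is tested only if the primary outcome is significant.

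The Discussion describes the margin differently: "A pragmatic approach was agreed in a noninferiority margin of 10% consolidation rate". It takes this from how far autograft controls and other healing technologies differed in two cited studies, one retrospective and one prospective, and adds: "This difference of 10% could be considered clinically irrelevant".

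Consolidation is a separate binary outcome in Table 1: "Bone consolidation is considered achieved when meeting the three following criteria". The three are radiographic bridging, low pain, and no further major surgery. Between the two doses it is compared only under SO2, by Fisher's exact test, without a margin.

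**The concern.** The Discussion's 10% is a difference in the proportion of patients who heal. The SO1 10% is a relative difference in the mean of a continuous X-ray score. They share a number but not an endpoint or a scale. A judgement that a 10-point difference in healing rate is unimportant says nothing about whether a 10% lower mean score is unimportant.

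SO1 is the trial's formal dose conclusion, and the Discussion presents the lower dose as easier and more sustainable to produce. Someone who reads a positive SO1 result through the Discussion would take it to exclude a 10-point loss in consolidation. The SO1 test does not do that.

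**Working it through.** **Inputs.** From section 3.1.2: CV 0.1349, ratio margin 0.90, true ratio 1.0, n = 36 per arm, one-sided alpha 2.5%. From section 3.1.1: control rate 74% and an expected gain of 20%, read here as points, so a planned rate of 94%. The printed mean of 0.113 and SD of 0.815 would give a CV of 0.815/0.113 = 7.2. They are read here as transposed (0.113/0.815 = 0.139, close to the stated CV). That reading is an assumption and is used only in the normal-model illustration and the conversion to score units.

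**1. Reproducing the plan's figure on the score ratio.**
- Log-scale SD = sqrt(ln(1 + 0.1349²)) = 0.1343.
- Margin = −ln(0.90) = 0.1054.
- Standard error = 0.1343 × sqrt(2/36) = 0.0317.
- Power = Φ(0.1054/0.0317 − 1.96) = 91.4%, or 90.7% with the noncentral t.

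This matches the stated figure of more than 90%, so the trial was sized on the score ratio.

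**2. The same arms with a 10-point rate margin.** Power = Φ(0.10/sqrt(2p(1−p)/36) − 1.96), with equal true rates p.
- p = 0.94: Φ(0.10/0.0560 − 1.96) = 43%.
- p = 0.90: Φ(0.10/0.0707 − 1.96) = 29%.

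For 90% power, n per arm = (1.96 + 1.2816)² × 2p(1−p)/0.10², which is 119 at 94% and 190 at 90%. So 36 per arm cannot have come from the margin that the Discussion describes.

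**3. The margin in score units.** At a mean of 0.815, 10% is 0.0815. With four evaluable cortices (16 points) that is 0.0815 × 16 = 1.3 cortical points. The article does not say whether such a loss matters.

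**4. Illustration of the rate loss at a true ratio of 0.90.** Assume that consolidation means a score above a cut-off, and choose the cut-off so that the high-dose rate is 94% (1.555 SD below the mean).
- Lognormal score, CV 0.1349: the shift is 0.1054/0.1343 = 0.785 SD. The low-dose rate is Φ(1.555 − 0.785) = 78%, a loss of 16 points.
- Normal score, mean 0.815, SD 0.113: the cut-off is 0.815 − 1.555 × 0.113 = 0.639 and the low-dose mean is 0.7335. With the same SD, the rate is Φ((0.7335 − 0.639)/0.113) = 80%, a loss of 14 points. With the same CV (SD 0.1017) it is 82%, a loss of 12 points.

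Under the lognormal version, a 10-point loss from 94% corresponds to a ratio of about 0.93, so true ratios between 0.90 and 0.93 satisfy the score margin but fail a 10-point rate margin. The result depends on the high-dose rate: the loss would be 21 points at 90%, 10.6 at 97% and 8.2 at 98%.

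**The case against.** The operative text is consistent. Section 3.1.2 and Table 1 agree on endpoint, scale and margin, and the sample size reproduces on that basis, so the test to be run is not in doubt. The divergence lies in the Discussion, which calls the margin pragmatic and concedes that its justification is a possible limitation. SO1 is a gated secondary test, already worded as radiological consolidation, and SO2 would show a loss in consolidation rate. The full protocol is not shown and may justify 0.90 in score units. All of this stands, and it limits the severity. It does not remove the contradiction: the one justification this article gives is on the wrong scale, and the admitted limitation does not mention the change of endpoint.

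A reader might infer that the score margin conceals a loss of 20 to 28 points. The documents do not support that. Such figures come from score cut-offs of 0.6875 and 0.75, which in the normal model imply high-dose rates of about 87% and 72%, below the planned 94%. No cut-off defines bridging either: three continuous cortices can score as little as 3+3+3+1 = 10/16 = 0.625, while 4+4+2+2 = 12/16 = 0.75 has only two. Consolidation also needs the pain and reintervention criteria, which the score does not measure.

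A reader might also infer that the Discussion promises a rate-noninferiority result that the trial is too small to deliver. It does not. It explains where a margin came from, and the 43% describes a test that nobody plans.

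**Conclusion.** The point holds as a contradiction in the text and should be fixed; it does not undermine the design. The endpoint and scale mismatch between the Discussion and section 3.1.2 with Table 1 needs no modelling. The power figures (about 91% on the score ratio, about 43% on a 10-point rate margin at 94%) show that the two margins are not interchangeable.

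The 12 to 16 point loss is an illustration. It rests on a threshold model, on the planned 94%, on the stated CV and, for the two smaller values, on the transposed mean and SD. It is the loss at the margin, not what a passing trial would be expected to show: with 36 per arm, success needs an observed ratio of about exp(−0.1054 + 1.994 × 0.0317) = 0.96. What follows is limited: SO1 success does not by itself rule out the 10-point rate loss that the Discussion calls clinically irrelevant. How large a rate loss it would allow is unknown.

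**What to change.** Reconcile the Discussion with section 3.1.2 and Table 1:

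- Remove the statement that the margin is a consolidation rate, and the justification that rests on it.
- Define SO1 success explicitly: the lower limit of the two-sided 95% CI for the G2b/G2a ratio of geometric mean REBORNE scores at 12 months lies above 0.90.
- Justify 0.90 in score units, for example in cortical points.
- Limit the SO1 claim, including in the Abstract, to a noninferior radiological score.
- Report beside it the 12-month G2b minus G2a difference in consolidation rate with its 95% CI, from the data already collected for SO2.

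This needs no new data, visits or patients. The cost is a narrower dose claim, and a rate interval that will be wide: at 94% in both arms its half-width is about 1.96 × 0.0560 = 11 points.

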## 5. Trial Status

The ORTHOUNION EU-H2020 project started on 1 January 2017. This trial received the EudraCT number 2015-000431-32, and the clinical protocol and IMP dossier (PEI 12-061) have been submitted for regulatory evaluation through VHP (9 January 2017) and authorized (19 April 2017) for France and Spain with a procedure number VHP1031-VHP2017004. The national phase at AEMPS (Spain) and ANSM (France) also completed the approval. Furthermore, the ethical committees of Hospital Universitario Puerta de Hierro Majadahonda of Madrid, Spain, and the Comité de Protections des Personnes Est IV of Strasbourg, France, also granted the authorization of the current clinical protocol. Germany and Italy are conducting a national phase evaluation with ongoing status.

## Figures and Tables

**Figure 1 fig1:**
[figure not shown]
CONSORT diagram of the ORTHOUNION clinical trial.

**Figure 2 fig2:**
[figure not shown]
Flow diagram of the ORTHOUNION clinical trial.

**Table 1 tab1:** Outcome measure and statistical analysis table.

Objective	Outcome measure	Time points of evaluation	Statistical analysis
Principal objective: to determine if the combined treatment of the ATMP, hBM-MSC + biomaterial (G2), is superior to the control, iliac crest autologous graft (G1), to obtain radiological and clinical bone consolidation	Bone consolidation is considered achieved when meeting the three following criteria: (1) Radiographic bone bridging: new bone formation across the fracture site visible in 3/4 cortices, on at least 3/4 views (2) Clinical healing: pain less than 3 in a NRS (0 to 10) for pain during full weight bearing and without weight bearing [36] (3) No further surgical major intervention (nail replacement, plate replacement, or replacement of all components of the previous surgery)	At 12 months after surgery	Superiority (target delta of 20%). Percentages will be estimated using a log-binomial regression model including the treatment, manufacturing site, and baseline value of the REBORNE scale as covariates. If unexpectedly the model does not fit, the Poisson long-link distribution function with a robust variance estimator will be used instead.

SO1: to determine if the low dose of hBM-MSC + biomaterial (G2b) is noninferior to high dose of hBM-MSC + biomaterial (G2a) to obtain radiological consolidation	Score calculated in xR images from REBORNE radiological scale following the formula: REBORNE score = ∑(internal, external, anterior, and posterior cortical value^∗^)/(4 × number of evaluable cortices)	At 12 months after surgery	Noninferiority (target delta of 10%). A log-transformed data of the values will be used in a mix model for repeated measurements, only if the primary outcome reaches statistical significance. Differences between arms will be estimated through adjusted means, standard errors, and its 95% CI

SO2: to compare the percentage of bone consolidation between G1 versus G2 and G2a versus G2b treatment arms	As defined in the principal objective	(i) G1/G2: at 6 and 24 months after surgery (ii) G2a/G2b: at 6, 12, and 24 months after surgery	Fisher's exact test

SO3: to compare the radiological consolidation between G1 versus G2 and G2a versus G2b treatment arms	As defined in SO1	At baseline and 6, 12, and 24 months after surgery	*t*-test or Mann–Whitney test

SO4: to compare pain with and without weight bearing using the G1 versus G2 and G2a versus G2b treatment arms	Pain score using the Numeric Rating Scale from 0 to 10, when 0 = no pain at all and 10 = worst pain ever	At baseline and 6, 12, and 24 months after surgery	Fisher's exact test Mann–Whitney test

SO5: to compare the rate of further surgical intervention at the callus site between G1 versus G2 and G2a versus G2b treatment arms	Further surgical intervention at the callus site is considered when nail replacement, plate replacement, or replacement of all components of the previous surgery are performed.	At 6, 12, and 24 months after surgery	Fisher's exact test

SO6: to compare the early and global complication rate between G1 versus G2 and G2a versus G2b treatment arms	Early (<3 months) and global complications included the following: (i) AE related to the product application process (surgical or other, including BM or ICA harvesting) (ii) Local heterotopic ossification (iii) Local bone resorption (iv) Local osteolysis (v) Local and general infection (vi) Vascular problems (ischemia, phlebitis) (vii) Neurological problems (viii) Unexpected events (e.g., hypersensitivity, immunological, and toxic) (ix) AE related to concomitant medication (e.g., anaesthetics)	At 6, 12, and 24 months after surgery	Fisher's exact test

SO7: to assess the safety of autologous hBM-MSCs between the G1 and G2 treatment arms	Safety understood as early or global complication rates and SAE rates, related to the use of hBM-MSCs	At 6, 12, and 24 months after surgery	Fisher's exact test

SO8: to identify the factors associated with bone regeneration between G1 versus G2 and G2a versus G2b treatment arms	Association outcomes (*β*, RR)	At 6, 12, and 24 months after surgery	Log-binomial regression model and mix model for repeated measurements^∗∗^

SO9: to compare the physical and mental health status between G1 versus G2 and G2a versus G2b treatment arms	SF-36 Health Survey score	At baseline and 6, 12, and 24 months after surgery	*t*-test or Mann–Whitney test

SO: secondary objective; NRS: Numeric Rating Scale; AE: adverse event. ^∗^Cortical value: 1 point if fracture is unchanged, 2 points if callus is noncontinuous, 3 points if callus is continuous but fracture is still apparent, 4 points if callus is with same density as cortical, and 0 points if noninterpretable or nonvisible. ^∗∗^Variables of interest: manufacturing centre (nominal), anatomical site of the fracture (femur, humerus, and tibia), sex (male, female), smoking habit (yes, no), and time since acute fracture (months).

**Table 2 tab2:** ORTHOUNION clinical trial inclusion/exclusion criteria.

*Inclusion criteria*
(1) Age 18 to 65, both sexes (2) Traumatic isolated closed or open Gustilo I and II, IIIA and IIIB humerus, tibial or femur diaphyseal, or metaphysodiaphyseal fracture with a status of atrophic, oligotrophic, or normotrophic nonunion. A nonunion is defined as a fracture not healed at least 9 months after the originating trauma that meets the following criteria: (i) Insufficient bone bridging to stabilize the fracture (ii) Insufficient bone biological activity in the fracture (iii) Failure of previous treatment (including bone grafting) (3) At least 9 months from acute fracture (4) Able to understand, accept, and sign informed consent (5) Medical health coverage (6) Able to understand and accept the study constraints
*Exclusion criteria*
(1) Hypertrophic nonunions (2) Segmental bone loss requiring specific therapy (bone transport, vascularized graft, large structural allograft, megaprosthesis, etc.) (3) Unrecovered vascular or neural injury (4) Other fractures causing interference with weight bearing (5) Visceral injuries or diseases interfering with callus formation (severe cranioencephalic trauma, etc.) (6) Active infection of any location and aetiology (7) Surgical contraindication of any cause (8) Pregnancy, breast-feeding women, and women who are of childbearing age and not practicing adequate birth control. The following methods are considered adequate: (i) Combined hormonal contraception (ii) Injected hormonal contraception (iii) Implanted hormonal contraception (iv) Progesterone-only hormonal contraception associated with inhibition of ovulation (v) Placement of an intrauterine device (IUD) (vi) Placement of intrauterine hormone-releasing system (IUS) (9) Malignant tumour (past history or concurrent disease) (except carcinoma in situ or basalioma in remission) (10) History of bone harvesting on iliac crest contraindicating new iliac crest bone graft harvesting or bone marrow collection (11) Insulin-dependent diabetes (12) Any evidence (confirmed by PCR) of active infection with HIV, hepatitis B, or hepatitis C (13) Any evidence of syphilis (14) Known allergies to products involved in the production process of MSC (15) Corticoid or immunosuppressive therapy more than one week in three months prior to study inclusion (16) Autoimmune inflammatory disease (17) Current treatment by bisphosphonates not stopped three months prior to study inclusion (18) Impossibility to meet at the appointments for the follow-up (19) Participation in another therapeutic trial in the previous 3 months (20) Second nonunion in case of bilateral or multiple nonunions (only one nonunion per patient will be included in the trial)

**Table 3 tab3:** ORTHOUNION arms of treatment description.

Study arm	Treatment	Dosage	Administration
G1: ICA (active comparator arm)	Iliac crest autograft	10 cc	Local administration under surgical procedure of nonunions
G2A: high dose of BM-MSC + B (experimental arm)	Expanded bone marrow mesenchymal stem cells, plus biomaterial (MBCP+)	200 × 10^6^ cells in 10 cc of biomaterial	
G2B: low dose of BM-MSC + B (experimental arm)		100 × 10^6^ cells in 10 cc of biomaterial

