Secondly, the conduction of the surgery will be the same as for bone autograft, except for the implantation of the composite (hBM-MSCs + biomaterial). The mixture will be prepared in the operating room as per protocol [20] and placed in the previously prepared area to be grafted. Each 5 mL cell product syringe is mixed with 5 cc of biomaterial (1-2 mm MBCP+ granules) filling the intergranular pores. The final mixture of the biomaterial and cells has a pasty consistency and it will be preferably introduced within the gap of the nonunion. Circumferential use of the material will only be performed when the bone gap is filled.

In both cases, a stable fixation of the fracture will be required. The use of an osteosynthesis system may include static or locked nail, locked or unlocked bone plate with screws, and/or external fixator (including the Ilizarov system) when other means are not adequate. Furthermore, the surgical technique will be reevaluated postoperatively by the clinical trial committee, to confirm the predefined criteria of a satisfactory surgical procedure (stable fixation and adequate augmentation) to validate the analysis of the case as per protocol. These criteria include absence of major complications after the procedure (intraoperative fracture, deviation, inadequate reduction, or other surgical gestures or interventions, except fibular osteotomy if required for compression or reduction of a tibial nonunion), presence of sufficient biomaterial or graft (filled nonunion gap, presence of sufficient graft/material in the fracture compression side and not in the tension side), and sufficient fixation (detecting immediately after surgery what could be considered an unstable fixation or unstable nail or other suboptimal techniques).

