### 3.2. Plan of Analysis

Primary and secondary endpoints and the statistical plan of analysis are described in Table 1. Five subgroups for analysis are declared: manufacturing site (Spain, France S1, France S2, Germany, and Italy); anatomical site: femur, humerus, and tibia; time (months) since acute fracture; smoking habits (yes/no); and sex (female/male). For these, Fisher's exact test for categorical variables, *t*-test or one-way ANOVA for Gaussian distributed variables, Mann–Whitney test and Kruskal-Wallis for non-Gaussian continuous variables will be used.

The plan of analysis will be tested in the following two populations of analysis: (a) modified full analysis set (mFAS) that will include all patients who have received treatment; (b) per protocol population (PP) that will include those patients in the mFAS set without major protocol deviations. Procedures to account for missing or spurious data will include patients whose information on consolidation is unknown at the end of the trial and will be considered failures, irrespectively, to the drop-out reason. With regard to the radiological consolidation, the baseline value will be used to impute the missing case; in case of treatment-related missing data, the missing case is not imputed otherwise. No formal imputations will be performed for the rest of variables, and the analyses will be based on the Available Data Only (ADO) approach.

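### Repeat grafting with the hardware left in place is not a failure under criterion 3 of the primary endpoint or under SO5, although augmentation is what the trial randomises

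*Protocol article*

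**What the plan says.** Table 1, principal objective, defines the primary endpoint as a composite in which every part must be met: "Bone consolidation is considered achieved when meeting the three following criteria". The parts are radiographic bridging, low pain, and the absence of further major surgery. The surgical part is "No further surgical major intervention (nail replacement, plate replacement, or replacement of all components of the previous surgery"). The pain part is "pain less than 3 in a NRS (0 to 10) for pain during full weight bearing and without weight bearing".

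SO5 is titled "SO5: to compare the rate of further surgical intervention at the callus site between G1 versus G2 and G2a versus G2b treatment arms". Its outcome measure is "Further surgical intervention at the callus site is considered when nail replacement, plate replacement, or replacement of all components of the previous surgery are performed". SO2 reuses the primary definition at 6 and 24 months for G1 versus G2, and at 6, 12 and 24 months for G2a versus G2b.

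Sections 2.5 and 2.5.2 make site preparation and the requirement for stable fixation common to the arms. Section 2.1 describes the trial as open. Section 2.3 has three independent clinicians adjudicate consolidation on blinded files under a charter that is not shown.

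Table 2 admits "humerus, tibial or femur diaphyseal, or metaphysodiaphyseal fracture" nonunions, and section 3.2 declares a subgroup by "anatomical site: femur, humerus, and tibia".

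**The concern.** The surgical criterion should catch patients who needed another bone-healing operation to reach union, so that the union is not credited to the randomised treatment. As printed it catches only exchange of hardware. A second graft, or a second biological augmentation with the nail or plate left in place, is in neither list. It is nevertheless the operation most closely tied to failure of the randomised component.

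Three features make this more than untidy wording:

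- SO5 cannot reveal the problem, because its definition has the same gap. It is also narrower than its own title, since re-grafting a nonunion is surgery at the callus site.
- Blinding the adjudication files does not help if the definition being applied does not count the event.
- In an open trial, re-operation is decided with the arm known. Section 2.4 calls iliac crest graft the standard of care, so a cell-treated patient could receive the comparator and then be counted as a cell success. The article describes no rescue pathway, so this is a possibility and not a stated practice.

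A smaller matter sits in criterion 2. It asks for pain during full weight bearing from every patient, and the article gives no upper-limb version although humerus nonunions are eligible.

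**Working it through.** **Is the list closed?** Criterion 3 gives three operations in parentheses with no wording that marks them as examples. SO5 then uses the same three as a definition. Its third item requires all components to be replaced, so it does not reach a re-graft that leaves the hardware in place. Re-grafting does not make a patient healed; it only fails to make the patient a failure. (External fixators are also allowed in section 2.5.2, "and/or external fixator (including the Ilizarov system) when other means are not adequate", and their exchange is not named either.)

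**Inputs from section 3.1.1:** G1 rate 0.74; G2 rate 0.74 + 0.20 = 0.94; 36 versus 72 patients; one-sided alpha 2.5% (z = 1.96); 5% loss; stated power more than 80%.

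**The plan's own figure.** The article does not name the test behind its calculation, so I used the pooled two-proportion test.

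- Pooled rate = (36 × 0.74 + 72 × 0.94)/108 = 0.8733.
- SE under the null = √[0.8733 × 0.1267 × (1/36 + 1/72)] = 0.0679.
- SE under the alternative = √[0.74 × 0.26/36 + 0.94 × 0.06/72] = 0.0783.
- Power = Φ[(0.20 − 1.96 × 0.0679)/0.0783] = 80.4%.

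Exact enumeration of the same test at 36/72 gives 82.0%. After 5% loss (about 34/68) the formula gives 78.3%. The stated power is broadly reproduced. The figures below use exact enumeration at 36/72.

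**Scenario A: a fraction r of failures in each arm is re-grafted and counted as healed.** The observed rate is p + r(1 − p). The values of r are assumptions.

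| r | G1 | G2 | Difference | Power |
|---|---|---|---|---|
| 0 | 0.740 | 0.940 | 20.0 points | 82% |
| 10% | 0.766 | 0.946 | 18.0 points | 77% |
| 20% | 0.792 | 0.952 | 16.0 points | 71% |

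The difference shrinks because G1 has more failures to rescue. For type I error, start from equal true rates of 74%, where the one-sided error is 2.8%. Equal contamination to 76.5% or 79% in both arms gives 2.95% or 3.0%, so there is essentially no inflation.

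**Scenario B: rescue in G2 only, equal true rates of 74%.**

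| Added to G2 | Share of G2's 26% failures | G1 vs G2 | One-sided error |
|---|---|---|---|
| 0 | 0 | 0.74 vs 0.74 | 2.8% |
| 2.5 points | 2.5/26 = 9.6% | 0.74 vs 0.765 | 5.4% |
| 5 points | 5/26 = 19% | 0.74 vs 0.79 | 9.7% |

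**Humerus item.** The documents give neither a humerus share nor a scoring rule, so no expected effect can be derived. Possible outcomes run from no loss, if a substitute item is used, to the worst case in which every humerus patient fails. At shares of 10/20/30% that worst case gives power of 59/41/29%. If 10% of otherwise healed humerus patients were lost to the item, power would be 79/77/75%.

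**The case against.** **The definition is the same in both arms.** Repeat grafting is possible in G1 too: section 2.5.1 mentions the contralateral crest when bone is insufficient, and Table 2 admits patients whose earlier grafting failed. A reader might infer that the endpoint is biased in favour of the cell product. The documents do not support that. With equal rescue, type I error hardly moves and the cost is power. This part of the objection stands.

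**Timing limits the numbers.** The failure must be recognised, re-operated without a hardware change, and then bridged with low pain, all within 12 months of the first surgery, while the trial's own nonunion definition needs at least 9 months. This argues for low rates of r at 12 months and stands as a limit on size. It does not correct the rule, however. The 9-month limit is an eligibility criterion and not a rule for re-operation, and the same definition serves the 24-month comparisons in SO2 and SO5, where there is more time.

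**The charter may settle it.** It may add re-grafting or an upper-limb rule. For the humerus item this is a fair answer. For criterion 3 it is weaker, because the article prints a specific list and repeats it as a definition. A charter that counted more would disagree with the published endpoint.

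**Humerus patients are not automatically failures.** A reader might join criterion 2 to the rule in section 3.2 that unknown consolidation is a failure. That rule is worded around drop-out and the end of the trial. It does not clearly cover a patient who attends and has one inapplicable item.

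**Conclusion.** The point holds for criterion 3 and SO5. As printed, a patient re-grafted or re-augmented at the nonunion site with the hardware retained can be a success of the augmentation that failed, and SO5 does not count the operation. This follows from the wording alone and depends on no assumption.

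The size does depend on assumptions, because no re-graft rate is given. Rescue of 10–20% of failures in both arms lowers power from 82% to about 77–71% with type I error near 3%. The rise in one-sided error to 5.4–9.7% needs rescue confined to G2, and is a conditional warning rather than an expected result.

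The humerus item is a secondary clarification. Criterion 2 and the eligibility criteria do not match, but the direction of any error is open. The power figures of 59/41/29% are a worst case and should not be read as the likely effect.

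The change is worth making before outcomes are adjudicated, since it concerns the primary endpoint and needs only wording.

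**What to change.** For outcome counting only, extend criterion 3 and the SO5 definition so that any further bone grafting, or cell or other biological augmentation, at the nonunion site before the assessment counts as further surgery, alongside the hardware replacements already listed. State in the same edit whether exchange of an external fixator counts. Use identical wording in the adjudication charter, so that the primary endpoint, SO2 and SO5 rest on one definition. Nothing here bears on when a patient should be re-operated.

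For criterion 2, state which item replaces full-weight-bearing pain when a humerus patient is scored, and use it in SO4 as well.

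The cost is a protocol and charter wording change, with the re-operation type recorded clearly enough to apply it. Success rates may be slightly lower in both arms.
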